###### **3.2.4. Exclusion Criteria: Individuals not eligible to be enrolled into this protocol are those who:**

1. Are pregnant or nursing, or are women of child bearing potential who are not practicing an effective means of birth control. Women of childbearing potential (i.e. assigned female at birth, fertile, following menarche and until becoming postmenopausal unless permanently sterile) must have a highly sensitive negative pregnancy test at study entry and prior to psilocybin session, and must agree to use adequate birth control through 10 days after the psilocybin session. Adequate birth control methods include intrauterine device (IUD), injected, implanted, intravaginal, or transdermal hormonal methods, abstinence, oral hormones plus a barrier contraception, vasectomized sole partner, or double barrier contraception. Two forms of contraception are required with any barrier method or oral hormones (e.g., condom plus diaphragm, condom or diaphragm plus spermicide, oral hormonal contraceptives plus spermicide or condom);
2. Have a history of or a current primary diagnosis of psychotic disorder, schizophrenia, delusional disorder, borderline personality disorder, schizoaffective disorder, bipolar disorder or, dissociative identity disorder;
3. Have evidence or history of coronary artery disease or cerebral or peripheral vascular disease, hepatic disease with abnormal liver enzymes, or any other medical disorder judged by the investigator to significantly increase the risk of psilocybin administration;
4. Have hypertension using the standard criteria of the American Heart Association (values of 140/90 or higher assessed on three separate occasions;
5. History of seizure disorder;
6. Uncontrolled insulin-dependent diabetes;
7. Recent stroke, intracranial or subarachnoid hemorrhage (< 1 year from signing of informed consent form [ICF]), recent myocardial infarction (< 1 year from signing of ICF), clinically significant arrhythmia (< 1 year from signing of ICF);
8. Have liver disease with the exception of asymptomatic subjects with Hepatitis C who have previously undergone evaluation and successful treatment;
9. Lifetime history of substance-induced psychosis;
10. Lifetime history of substance use disorder with a hallucinogen;
11. History of alcohol use disorder in the past 3 months;
12. Would present a serious suicide risk, as determined through a psychiatric interview, responses to Columbia Suicide Severity Rating Scale (C-SSRS) (cut-off ⩾3 points) and through the clinical judgment of the investigator, or who, in the judgment of the investigator, are likely to require hospitalization during the course of the study;
13. Would present a serious risk to others as established through clinical interview and contact with treating psychiatrist;
14. Have used psilocybin at least once within 12 months of the psilocybin session;
15. Require ongoing concomitant therapy with a psychiatric drug;
16. Active substance abuse or dependence for any substance save caffeine or nicotine in the past 3 months;
17. Are not able to give adequate informed consent;
18. Positive urine drug screen for illicit drugs or drugs of abuse at screening (any positive urine drug test will be reviewed with participants to determine the pattern of use and eligibility will be determined at the investigator’s discretion);
19. Current enrolment in any investigational drug or device study or participation in such within 30 days of screening;
20. Abnormal and clinically significant results on the physical examination, vital signs, electrocardiogram, or laboratory tests at screening;
21. Any other clinically significant cardiovascular, pulmonary, gastrointestinal, hepatic, renal or any other major concurrent illness or concerns that in the opinion of the investigator, may interfere with the interpretation of the study results or constitute a health risk for the participant if he/she takes part in the study;
22. Have any current problem or a history of substance abuse which, in the opinion of the investigator or medical monitor, might interfere with participation in the protocol;
23. First degree family history of bipolar I disorder, schizophrenia or any psychotic disorders, including bipolar disorder with psychotic features;
24. Unable to accurately and completely communicate study information, answer questions about the study;
25. Have evidence or history of moderate and severe renal disease.

###### **3.2.5. Withdrawal Criteria**

Participants are free to withdraw their consent and/or end their participation in the research study at any time without penalty or loss of benefits or treatment to which they are otherwise entitled. Participants may be withdrawn from the study by the study’s doctor if they feel that it is in their best interest.

Participants may also be discontinued if:

- They fail to adhere to the study’s responsibilities;
- The participant meets any exclusion criteria (either newly developed or not previously recognized);
- They present with any AE or unknown allergic reaction to psilocybin;
- Anything, in the opinion of the investigator, that would place the participant at increased risk or preclude the participant’s full compliance with or completion of the study;
- They are pregnant or of childbearing potential and not willing to use an approved method of contraception during the study.

If a participant experiences an AE they will receive the necessary treatments to alleviate any untoward event and will be monitored by the study physician until it is safe for them to be discharged. Participants will be followed up the next day to monitor the progression of their condition. Data from a participant who has been withdrawn will be collected up to the next day after the withdrawal to ensure that the participant has no delayed complications. If a participant withdraws from the study at any time, the reasons for withdrawal will be collected and documented as part of the feasibility outcome for this study. Data collected up to the point of withdrawal will be used for analysis.

If a subject’s participation in the study is terminated prematurely for any reason, the reason for early discontinuation should be thoroughly documented in the case report form (CRF), and the end-of-study assessments should be completed where possible. A termination CRF page should be completed for every participant who receives a dose of psilocybin.

Reasons for a participant’s premature study discontinuation may be categorized as follows:

- Screen Failure: The participant signed the ICF but was deemed ineligible for the study during the screening process;
- AE: An untoward clinical or laboratory event that, in the medical opinion of the investigator, are grounds for early study termination to protect the best interests of the participant. This includes serious and non serious AEs, regardless of their causal relationship to psilocybin;
- Withdrawal of Consent: The participant withdrew their consent from the study after signing the ICF. Every reasonable effort should be made by study personnel to determine the cause for withdrawal of consent, and the reason should be documented accordingly in the participant's CRF;
- Protocol Violation: The participant’s conduct failed to meet protocol entry criteria, or the participant did not meet study requirements (i.e., non-compliance). The protocol violation necessitated early termination from the study;
- Lost to Follow-Up: The participant stopped attending study visits, and study personnel were unable to contact the participant. The study personnel should make a reasonable attempt to establish contact with the participant if they become lost to follow-up;
- Other: The participant was discontinued for a reason other than those listed above.

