###### **4.1.9. Adverse Event Follow-up**

All AEs will be followed until resolved or stable and the outcome documented on the CRF. If the investigator detects an AE in a study participant after the last scheduled follow-up visit and considers the event possibly related or related to prior study treatment, the investigator will document it.

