###### **4.1.10. Serious Adverse Events**

A serious adverse event is an AE that fulfills one or more of the following criteria:

- results in death
- is life-threatening
- requires in-patient hospitalization or prolongation of existing hospitalization
- results in persistent or significant disability or incapacity
- is a congenital abnormality or birth defect in the offspring of a participant who received the investigational product
- is an important medical event that may jeopardize the patient or may require medical intervention to prevent one of the outcomes listed above.

Any serious, untoward event that may occur subsequent to the reporting period that the investigator assessed as related to psilocybin should also be reported and managed as an SAE. The investigator should follow participants with AEs until the event has resolved or the condition has stabilized. In case of unresolved AEs, including significant abnormal clinical laboratory values at the end of study assessment, these events will be followed until resolution or until they become clinically not relevant.

Disability/incapacitating: An AE is incapacitating or disabling if the experience results in a substantial and/or permanent disruption of the participant's ability to carry out normal life functions.

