###### **7. Statistics**

###### **7.1. General Procedures and Statistical Methods**

Feasibility outcomes will be reported with descriptive statistics (i.e., counts and proportions). A minimum of 2-3 participants per month (at our single site) will be considered a sufficient recruitment rate to indicate the feasibility of a future larger multi-site trial. We will estimate the proportions of participants adherent with the protocol, that withdraw, and for data completion with a 95% CI. A full trial with this design will be deemed feasible if the lower 95% confidence limit for the rates of adherence and data completion are **≥** 80%, and if the upper limit of 95% confidence interval for the withdrawal rate is ≤ 20%. Frequencies and proportions of AEs and serious AEs will be tabulated for the total sample for each AE type. For continuous outcomes, we will report the means and standard deviations of the score and its change from baseline until the end of treatment and over the follow-up visits. We will estimate the standard deviation of PTSD severity [CAPS-5] and its within person correlation between the baseline and the end of treatment scores. The study will examine the effect size associated with psilocybin-assisted CPT in participants with PTSD, including the durability of effects on PTSD symptoms. The main analysis will be a comparison of PTSD symptoms before and after treatment. There will be analyses of changes in symptoms of depression, psychological functioning, sleep quality and PTSD severity. In week 2, the primary endpoint assessment will take place for all subjects. An independent rater not involved in therapy will administer or collect some outcome measures, and others will be based on subjects’ self-report. Baseline will be compared to the primary end point and follow up time points. This study will provide data on the impact of psilocybin in conjunction with massed CPT. Based on the outcomes, this study will primarily detect effects due to psilocybin-assisted CPT on PTSD symptoms through calculating effect sizes and significance testing. A Wilcoxon signed rank test comparing Clinician-Administered PTSD Scale for DSM-5 (CAPS-5) scores from the baseline to the primary endpoint will be the main analysis. Durability of effects will be examined by comparing changes from baseline to the assessments at 1 until 12 weeks after the final CPT session (day 7) for each PTSD subject using Friedman test, which is a non-parametric test method for repeated measures. Effects on depression symptoms, psychological functioning, trauma-related beliefs and sleep quality will also be assessed for exploratory purposes. Changes in these measures will be compared from baseline to primary endpoint for participants using Wilcoxon signed rank tests. Analyses will examine changes from baseline up to week 13 using Friedman tests. Effect sizes for the psilocybin-assisted CPT will be calculated at the primary endpoint and follow-up time points.

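### Section 3.2.5 stops data collection the day after withdrawal, although any AE can lead to discontinuation and sections 4, 4.1.9 and 4.1.10 require longer follow-up

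*Protocol*

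**What the plan says.** Protocol section 3.2.5 allows discontinuation for any AE, among other grounds. On what follows it states: "Data from a participant who has been withdrawn will be collected up to the next day after the withdrawal". The same sentence gives the purpose, with collection running to the day "after the withdrawal to ensure that the participant has no delayed complications". The paragraph ends: "Data collected up to the point of withdrawal will be used for analysis". The next paragraph, on premature termination for any reason, adds that "the end-of-study assessments should be completed where possible", without fixing a time.

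The safety sections run longer. Section 4.1.9: "All AEs will be followed until resolved or stable and the outcome documented on the CRF". Section 4.1.10: "The investigator should follow participants with AEs until the event has resolved or the condition has stabilized". The list that opens section 4 has events leading to withdrawal, and events tied to a change in psychiatric status, collected throughout the study. Section 4.1.6 collects AEs from Day 1 of the treatment week to the end of the study.

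For efficacy, section 7.1 states "In week 2, the primary endpoint assessment will take place for all subjects", and says that a Wilcoxon signed-rank test of CAPS-5 "scores from the baseline to the primary endpoint will be the main analysis".

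**The concern.** A participant discontinued because of an unresolved AE falls under two instructions at once. Section 3.2.5 ends collection the next day. Sections 4, 4.1.9 and 4.1.10 continue it. Staff could follow either and be in line with the protocol.

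The participants affected may be those who most need observation. Section 3.2.5 also allows discontinuation when an exclusion criterion newly develops, and exclusion criterion 12 is serious suicide risk, including a C-SSRS cut-off of 3 or more. Section 3.9 requires withdrawal when standard of care calls for a change in psychotropic medication. Such a participant could leave scheduled C-SSRS monitoring one day later.

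Section 4.1.9 alone does not close the gap. It follows an AE that is already known. It schedules no C-SSRS and no Week 2 CAPS-5.

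**Working it through.** The protocol gives no figure to reproduce here. The check has two parts: the rules set side by side, and a count from Table 2.

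**Rules**

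| Section | Applies to | Collection ends |
|---|---|---|
| 3.2.5, one-day sentence | withdrawn participants | day after withdrawal |
| 3.2.5, next paragraph | premature termination for any reason | end-of-study assessments, if possible |
| 4, opening list | events leading to withdrawal | end of study |
| 4.1.9 | all AEs | resolved or stable |
| 4.1.10 | participants with AEs | resolved or stabilised |

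The first row conflicts with the last three for anyone withdrawn with an ongoing AE. No order of precedence is stated.

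**Inputs from Table 2**

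- AE checks from Day 1: Days 1, 2, 3 pre-dose, 3 post-dose, 4, 5, 6 and 7 make 8. Weeks 2 to 13 make 12. Total 8 + 12 = 20.
- C-SSRS since last visit, from Day 1: the same columns, 20.
- Post-baseline CAPS-5: Day 7 and Weeks 2, 5 and 13, so 4. The list in section 3.1 leaves out Week 2. I follow Table 2, which agrees with section 7.1.
- Section 4.2 places the end-of-study visit at Week 13. That visit carries one AE check, one C-SSRS and one CAPS-5, so if it takes place it recovers one of each.

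**Losses if the one-day sentence is followed**

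| Discontinued | Last data | AE checks lost, and C-SSRS lost (each of 20) | CAPS-5 lost (of 4) |
|---|---|---|---|
| Day 3 | Day 4 | Days 5–7 (3) + 12 = 15; 15 − 1 = 14 with the end-of-study visit | 4; or 4 − 1 = 3 |
| Just after Day 7 | next day | 12; 12 − 1 = 11 with the visit | Weeks 2, 5, 13 = 3; or 3 − 1 = 2 |

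In both cases the Week 2 CAPS-5 is lost. Each such loss removes 1 of 15 baseline-to-Week-2 pairs, 1/15 = 6.7%.

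**How often the clause may be used.** With 15 participants and independent withdrawals:

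- At the 10% dropout hypothesised in 2.6.1: expected 15 × 0.10 = 1.5; chance of at least one 1 − 0.9^15 = 79.4%.
- At the 20% threshold in 3.10.1: expected 15 × 0.20 = 3; chance of at least one 1 − 0.8^15 = 96.5%.

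Both rates are all-cause. They include withdrawn consent and loss to follow-up, so they do not give the rate of investigator discontinuation.

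**The case against.** The best reply is that the one-day sentence sets a floor. It stands in a paragraph on acute AE handling, its stated purpose is to check for delayed complications, and a hard stop sits badly with the request for end-of-study assessments that follows. The safety sections are also more specific, and section 4 covers events that lead to withdrawal. This shows what the authors may have meant. It does not settle the text, because the sentence gives an end to collection and no minimum. The end-of-study request is optional and secures neither the interim C-SSRS nor the Week 2 CAPS-5.

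A reader might infer that 3.2.5 directly contradicts 7.1, because 7.1 refers to all subjects at Week 2. The documents do not support that. The sentence in 7.1 mainly sets timing and does not promise that withdrawn participants will attend.

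A reader might also put a size on the bias in mean CAPS-5 change. If k of 15 lacked a Week 2 score and had zero change, the observed mean would overstate the all-participant mean by 15/(15 − k) − 1, which is 7.1%, 15.4% and 25.0% for k = 1, 2 and 3. If they changed like the others, it would be 0%. Nothing in the protocol supports zero change. Nor is three a maximum: the 20% in 3.10.1 is a threshold for calling the design feasible and puts no cap on withdrawals.

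Three further points stand. How the tests treat missing scores may be left to the SAP. CAPS-5 is a secondary outcome (3.10.2). And 4.2 permits lorazepam up to 2 mg a day and rescue medication, so mandatory withdrawal under 3.9 is narrower than it first appears. What is collected after withdrawal remains a matter for the protocol.

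**Conclusion.** The contradiction between 3.2.5 and sections 4, 4.1.9 and 4.1.10 is real and should be removed. Taken literally, 3.2.5 ends scheduled safety observation at a cost of 14 to 15 of 20 AE checks and the same number of C-SSRS checks for a Day 3 discontinuation, or 11 to 12 of 20 just after Day 7. The CAPS-5 losses are 3 to 4 of 4 and 2 to 3 of 4. These counts assume that the one-day sentence is followed as written, and each range depends on whether the end-of-study assessment takes place.

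The effect on the signed-rank test is secondary. Its size is unknown, since it depends on how many are discontinued before Week 2 and how they fare. The withdrawal rate, a primary feasibility measure, is unaffected, because these participants count as withdrawn either way. The percentage with AEs could be understated only for someone withdrawn for another reason whose first AE comes later.

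**What to change.** Replace the one-day sentence in 3.2.5 with:

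*The next-day contact is a minimum. Unless consent is withdrawn, participants discontinued by the investigator continue scheduled AE and C-SSRS follow-up, with AEs followed as in 4.1.9, and the Week 2 CAPS-5 is sought. These data are used in the analysis, with any restarted psychotropic medication recorded. These participants still count as withdrawn for the 20% criterion.*

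The sentence in 3.2.5 that limits analysis to data up to withdrawal should be brought into line.

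The cost is a short amendment, with REB and, as applicable, Health Canada approval under section 6.6. No visit is added beyond Table 2. A Day 3 discontinuation leaves 3 + 12 = 15 contact days already in the schedule, and section 3.13.9 makes Weeks 2 to 12 virtual. Participants remain free to restart medication that 4.3 bars until the end of the study. The drawback is that some CAPS-5 scores will be taken on restarted medication, and the record makes them identifiable.

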###### **3.2.6. Deviation from Inclusion/Exclusion Criteria**

No deviations will be permitted from the inclusion or exclusion criteria.

###### **3.3. Participant Screening**

Participants will be screened at the Interventional Psychiatry Program at St. Michael’s Hospital, Unity Health Toronto. Before screening, participants will sign a print version of the ICF. Then, participants will undergo screening to confirm eligibility. Participants who are not eligible during the screening will be allowed to re-try on a case by case basis.

###### **3.4. Recruitment**

Participants will be recruited from Interventional Psychiatry Program, St. Michael’s Hospital and referred from PTSD Psychotherapy Program lead by [name] at Toronto Metropolitan University. The target recruitment rate is at least 2-3 participants per month for a total of 15 subjects recruited over 7 months. Participants who experience chronic PTSD and are interested in the study will be directed to the study coordinator. The study coordinator will then reach out to the potential participants through a phone or Zoom meeting, where they will be provided with a brief background about the study and the required time commitment before scheduling the screening visit.

###### **3.5. Intervention**

Participants will receive 25 mg (five capsules of 5mg) of psilocybin. The dosing session will be scheduled on day 3 of the treatment week. The study coordinator and the therapist with whom they have been completing CPT sessions will be present on site for the session. After the acute effects of the psilocybin pass, participants will be evaluated for safety and discharged home with a chaperone. The participant should have a light breakfast two hours before receiving psilocybin. Under the direct supervision of the therapist, 25 mg (5 capsules of 5 mg) of psilocybin will be swallowed. The dosing session will take 6-8 hours. Psilocybin effects usually begin 20-30 minutes after administration and peak at 90-120 minutes post-administration. Within 5-6 hours, the effects eventually subside. To minimize distraction and interruption, the participant is instructed to lie down on a couch in a room with low lighting after taking the psilocybin. To encourage inward reflection, the participant will listen to a pre-programmed selection of music during the session. A therapist specialized in providing reassurance and a safe environment will accompany the participant until the effects of the dose have passed. A physician will be available on site in case of an emergency. Moreover, the study coordinator will be at the study center during the psilocybin dosing session to support the therapist if needed. The participant must remain in the room for the whole duration of the session, regardless of intensity. Unless the participant has to communicate discomfort, ask for support from the therapist, or use the toilet, the participant should stay lying down. The therapist is to check-in on how the participant is doing every 1-2 hours following dosing. The participant will be served a light meal and fruit. The therapist will review the psilocybin administration experience with the participant 5 to 6 hours after dosing. When the therapist determines the acute effects of the psilocybin have subsided, which should occur between 6 and 8 hours after taking the dose, the participant will be discharged. The participant will be discharged from the study setting into the care of a responsible person (such as a family, friend, or chaperone) who will accompany the participant home and monitor them for 24 hours after the dose was given. Research coordinator will complete pre dose and post dose assessments. Post dose assessment will be completed after acute effects of psilocybin are resolved. Upon completion of the post-dose assessments, the participant will be assessed for safe discharge under the supervision of a designated chaperone.
